## Abstract

**Background:**

Physical inactivity is a leading preventable cause of chronic disease and premature death globally, yet over half of the adult Australian population is inactive. To address this, web-based physical activity interventions, which have the potential to reach large numbers of users at low costs, have received considerable attention. To fully realise the potential of such interventions, there is a need to further increase their appeal to boost engagement and retention, and sustain intervention effects over longer periods of time. This randomised controlled trial aims to evaluate the efficacy of a gamified physical activity intervention that connects users to each other via Facebook and is delivered via a mobile app.

**Methods:**

The study is a three-group, cluster-RCT. Four hundred and forty (440) inactive Australian adults who use Facebook at least weekly will be recruited in clusters of three to eight existing Facebook friends. Participant clusters will be randomly allocated to one of three conditions: (1) waitlist control condition, (2) basic experimental condition (pedometer plus basic app with no social and gamification features), or (3) socially-enhanced experimental condition (pedometer plus app with social and gamification features). Participants will undertake assessments at baseline, three and nine months. The primary outcome is change in total daily minutes of moderate-to-vigorous physical activity at three months measured objectively using GENEActive accelerometers [Activeinsights Ltd., UK]. Secondary outcomes include self-reported physical activity, depression and anxiety, wellbeing, quality of life, social-cognitive theory constructs and app usage and engagement.

**Discussion:**

The current study will incorporate novel social and gamification elements in order to examine whether the inclusion of these components increases the efficacy of app-based physical activity interventions. The findings will be used to guide the development and increase the effectiveness of future health behaviour interventions.

**Trial registration:**

This trial was registered with the Australian and New Zealand Clinical Trial Registry (ACTRN12617000113358, date of registration 23 January, 2017).

## Background

Physical inactivity is the fourth leading behavioural risk factor contributing to the population attributable burden of disease, as it is strongly associated with physical and mental health problems and continues to have a significant economic burden [1–4]. Current Australian guidelines recommend adults complete at least 150 min of physical activity per week at a moderate-to-vigorous intensity to reduce the risk of developing chronic diseases such as cardiovascular diseases and diabetes [2, 5, 6], and for a myriad of additional benefits such as improved muscular and cardiorespiratory fitness, stronger bones and mental health [5, 7]. Yet almost half of the Australian adult population do not meet these guidelines [2, 8].

Smartphone and social media use have become ingrained into everyday life and together offer a feasible, accessible and innovative platform from which to launch a physical activity intervention [9–12]. Facebook attracts 15 million Australian users each month and 10 million every day [13], 90% of whom log on from an application (‘app’) on their mobile device [14, 15]. Health behaviours have been found to spread through individuals’ social networks, by way of real life social support [16–18] and this may be true for online social networks [19–23]. Two recent systematic reviews suggest that online social networks may successfully be harnessed to promote health behaviour change [9, 24]. Further exploration is warranted as to date such interventions typically report low rates of participant engagement with intervention components and low rates of retention, potentially limiting their effectiveness [9, 24, 25]. Participant engagement has been positively associated with both increased retention and intervention effects [24, 26–30]. Novel approaches to increase the appeal of, and therefore engagement with, interventions are needed. Gamification, the application of game design elements such as rewards, challenges and competition, teamwork, point scoring and leader boards, into a traditionally non-game environment is one such approach [31, 32]. A recent systematic review suggests that gamification is effective in increasing engagement with online programs [33] and two reviews of commercially available health and fitness apps suggested that gamification has the potential to enhance positive behaviour change [34, 35]. Recent health behaviour change studies incorporating gamification elements have produced similarly promising results [27, 36, 37].

App-based physical activity interventions that incorporate gamification have the potential to reach large numbers of users at relatively low costs [38]. The available evidence highlights a need to enhance user engagement to realise the potential impact of this approach. As such, the current study will assess the efficacy of an app-based intervention that incorporates social media and gamification elements in a three-group cluster-randomised controlled trial (RCT).

### Objectives

The primary aim of this study is to examine whether using the ‘Active Team’ smartphone app, a purpose-built, gamified physical activity intervention that connects users to each other via Facebook, leads to a significant difference in physical activity levels relative to a basic app-based experimental condition and a waitlist control condition after three months.

Secondary aims are to examine whether: (1) differences in physical activity levels between experimental conditions and waitlist control condition are sustained across a nine-month follow up, (2) there are differences between the experimental conditions and waitlist control condition in changes to quality of life, depression and anxiety, and wellbeing after three and nine months, (3) to examine potential moderating effects of sociodemographic variables of increasing physical activity, (4) to examine engagement with the Active Team app, and (5) to examine social-cognitive constructs as potential mediators of the intervention efficacy in increasing physical activity levels.

## Methods

### Study design

The study is a parallel, three-group cluster-RCT with assessments at baseline, three and nine months. Ethical approval for the study was obtained from the Human Research Ethics Committee of the University of South Australia and the trial is registered with the Australian and New Zealand Clinical Trial Registry, protocol number: ACTRN12617000113358. The study is funded by a Project Grant from the National Health and Medical Research Council of Australia. The conduct and reporting of the trial will adhere to the Consolidated Standards of Reporting Trials (CONSORT) guidelines [39]. All participants will provide informed consent online prior to commencing the study.

### Participants

#### Eligibility criteria

Participants will be aged 18 to 65 years, use Facebook at least weekly, be fluent in English, live anywhere in Australia, currently complete less than 150 min of moderate-to-vigorous physical activity (MVPA) per week and be able to assemble a cluster of minimum three to maximum eight Facebook friends who also meet the eligibility criteria and are willing to join the study. Participants who self-report as being unable to safely increase their physical activity levels will be excluded from the study.

#### Recruitment

Four hundred and forty (440) participants will be recruited over a period of nine months. Recruitment strategies include flyers placed around local university campuses, paid Facebook advertising (including a campaign targeted specifically to men, as previous studies have had difficulties recruiting men for this type of intervention [9]), and free advertisements placed on community group Facebook pages. All advertisements will direct participants to a website containing further study details including full eligibility criteria and a form to register interest.

#### Procedure

Figure 1 provides an overview of the study procedure.

**Fig. 1 Fig1:**
[figure not shown]
Study Procedure Flowchart

All participants who register interest will be contacted via email, and followed up via phone. Participants will be asked to complete an online eligibility screening and informed consent process that is embedded within the baseline survey. Participants who meet the eligibility criteria and provide informed consent will be directed to the full baseline survey, which takes approximately 15 min to complete.

As the intervention seeks to use existing social networks to promote physical activity, the study will recruit clusters of between three to eight participants who are already friends on Facebook. Initial participants will be guided through the process of downloading the Active Team app and using it to send invitations to join the study to their selected friends. The invitation will appear as a notification on the recipients’ Facebook profile and those who click on the notification will be automatically directed to their respective app store. New participants joining the study in this way will register their interest via the app and will also be contacted via email, and followed up via phone.

Upon completion of the baseline survey and assembly into a cluster, a wrist-worn accelerometer (GENEActiv) will be posted to each participant in the cluster with instructions to wear the device 24 h a day for seven days before posting it back in a reply-paid envelope. Once all members of a cluster have completed baseline assessments (survey and accelerometry) the cluster will be randomly allocated to either a waitlist control condition, basic experimental condition or socially-enhanced experimental condition on a 1:1:1 allocation ratio using permuted blocks with block sizes of 9, 12 or 15, to ensure a balance of clusters across experimental conditions throughout the trial. An independent allocation officer will determine block size and allocation schedule using a random number generator and a computer generated randomisation schedule. Block size and block allocation sequence will be concealed from the person enrolling the participants.

The assessments procedure will be repeated at three and nine months. Participants will be provided with a small honorarium ($AUD75, about $US55) upon completion of assessments at the final time point.

#### Sample size and statistical power

Sample size calculations are based on the primary outcome measure of total daily minutes of MVPA measured using accelerometry. The pilot study (*n =* 110) of the Active Team app [11] found a small to medium effect size difference (Cohen’s d = 0.39) relative to a waitlist control condition from baseline to eight week follow up. For the current study, a similar effect size difference is anticipated between the socially-enhanced experimental condition and the waitlist control condition. A smaller effect size difference is anticipated between the socially-enhanced experimental condition and the basic experimental condition, hence the larger sample size. Based on sample size calculations (α = 0.05, β = 0.2), a sample of 440 will be sufficient to detect a small effect size (Cohen’s f^2^ = 0.13, Cohen’s d = 0.25) for between-group difference on the primary outcome if one exists.

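### The stated 80% power for 440 participants is not shown to hold for this cluster-randomised design: the calculation shows no allowance for clustering or loss, and 440 does not follow from d = 0.25 for the contrast said to drive it

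*Protocol article*

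**What the plan says.** The protocol article, under Sample size and statistical power, starts from a pilot that "found a small to medium effect size difference (Cohen’s d = 0.39) relative to a waitlist control condition". It then explains why the trial is larger than that effect would need: "A smaller effect size difference is anticipated between the socially-enhanced experimental condition and the basic experimental condition, hence the larger sample size". The conclusion is "Based on sample size calculations (α = 0.05, β = 0.2), a sample of 440 will be sufficient". The target attached to that number is worded as follows: "to detect a small effect size (Cohen’s f^2^ = 0.13, Cohen’s d = 0.25) for between-group difference on the primary outcome". That section gives no intracluster correlation, cluster size, number of clusters, baseline correlation, attrition figure or named test.

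Under Procedure, "the study will recruit clusters of between three to eight participants who are already friends on Facebook", and clusters are allocated "on a 1:1:1 allocation ratio using permuted blocks with block sizes of 9, 12 or 15". Under Recruitment, "Four hundred and forty (440) participants will be recruited over a period of nine months". The number said to be sufficient and the number to be enrolled are therefore the same. The Background notes that interventions of this kind have shown "low rates of retention, potentially limiting their effectiveness".

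**The concern.** Members of a friend group share habits and surroundings, and the enhanced app is meant to work through their influence on one another. Zero correlation within clusters is therefore not a natural assumption. Positive correlation makes 440 people worth fewer than 440 independent observations, and every participant without three-month accelerometry reduces the number further. A calculation that shows neither adjustment has not been shown to describe this trial.

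The comparison most exposed is enhanced versus basic, the one that isolates the social and gamification features. If readers believe it had 80% power at d = 0.25 when it had much less, a null result could be taken as evidence that those features add nothing.

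**Working it through.** **Inputs from the protocol article:** alpha 0.05 (taken as two-sided; sidedness is not stated), beta 0.2, d = 0.25 and 0.39, 440 recruited, three arms 1:1:1 (440/3 = 146.7 per arm), clusters of 3 to 8.

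**Assumed, because the article gives no figure:** mean cluster size m = 5 to 5.5, ICC 0.01 to 0.10, loss at three months 0 or 20%.

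**Step 1. Can 440 be reproduced?** For two means, n per arm = 2(1.96 + 0.842)²/0.25² ≈ 251, or 252 with the t-distribution. That is 756 for three arms (one-sided: 198 per arm, 594). A one-way three-group ANOVA needs 620 at f = 0.125 (which is d/2) or 574 at f = 0.13. The printed f² = 0.13 taken literally needs only 78 and does not match d = 0.25, for which f² = 0.0156. None of these gives 440.

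**Step 2. Problem (a): independent observations, complete data, no baseline adjustment.**
- Power at d = 0.25: Φ(0.25·√(146.7/2) − 1.96) = Φ(0.18) ≈ 57%.
- Detectable d at 80% power: 2.80·√(2/146.7) ≈ 0.33.
- A pairwise ANCOVA reaches 80% when 1 − r² = 146.7/251.2 = 0.584, so r ≈ 0.65. No baseline correlation is stated.
- At d = 0.39 (enhanced versus waitlist), power is about 92%.

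About 23 points (80 − 57) are missing here, before clustering or loss enters.

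**Step 3. Problem (b): grant 440 exactly 80% under independence and full follow-up, then adjust.** DE = 1 + (m − 1)·ICC; power = Φ(2.80·√((1 − loss)/DE) − 1.96).

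| m | ICC | DE | No loss | 20% loss |
|---|---|---|---|---|
| 5 | 0.05 | 1.20 | 72.5% | 62.8% |
| 5.5 | 0.05 | 1.225 | 71.6% | 61.9% |
| 5.5 | 0.01 | 1.045 | 78.2% | 68.8% |

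The last column keeps m fixed. If loss also shrinks the clusters, so that DE = 1 + (0.8m − 1)·ICC, the two ICC 0.05 rows become 64.7% and 63.9%. A fair summary is 63% to 64%. At ICC 0.01 without loss, clusters of 3 to 8 cost 1 to 3 points.

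**Step 4. Both problems together, no baseline adjustment, m = 5.** At ICC 0.05 and 20% loss the effective number per arm is 146.7 × 0.8/1.20 = 97.8. Power at d = 0.25 is then about 42%, and the detectable d is 2.80·√(2/97.8) ≈ 0.40. A baseline correlation of about 0.78 would restore 80% at d = 0.25. For d = 0.39 with 20% loss, power is about 82% at ICC 0.02 and 71% at ICC 0.10.

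**The case against.** The strongest reply is that a journal article condenses, so the ICC and attrition figures may sit in a fuller document. That would excuse an unreported input, and it limits what can be claimed. It does not explain how 440 follows from d = 0.25 for a pairwise contrast, since simple formulas already need more than 440 before any inflation.

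A second reply is that the article prints an f-type effect size and plans mixed modelling over three time points, so a repeated-measures formula may have been used. Some of these do give smaller totals. With three groups, three measurements and correlations of 0.3 to 0.5, the between-factor test needs 308 to 415 and the group-by-time interaction 121 to 181 (f = 0.125 to 0.13). At 308 the margin is 440/308 = 1.43, enough for a design effect of 1.14 with 20% loss (1.14/0.8 = 1.43). This stands as a limit: a reader might infer that 440 has no margin under any method, or that r = 0.65 is needed whatever the test, and the document does not support either. But no such method is stated, and an omnibus test over all three arms is not the enhanced-versus-basic contrast.

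A reader might also credit the whole fall from 80% to about 42% to clustering and loss. That is wrong too: about 23 points come from step 2. From 57%, an ICC of 0.05 at m = 5 takes about 7 points and 20% loss about 8 more.

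Finally, retention may be better than in earlier studies, since accelerometer wear can be repeated up to three times and an honorarium is paid at the final assessment. No loss figure is given either way.

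**Conclusion.** The concern holds in this form: the claim of 80% power at d = 0.25 is not shown to belong to a trial that randomises friend groups and recruits exactly 440.

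Problem (a) rests on the article's own figures and a two-sided pairwise test: about 57% power without baseline adjustment. Problem (b) is conditional on assumed values. It is small at ICC 0.01 with full follow-up, and material at ICC 0.05 with 20% loss even when 440 is granted its 80%.

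The weakness falls mainly on enhanced versus basic; enhanced versus waitlist at the pilot effect is less affected. Low power does not by itself bias the estimates, and nothing here shows the planned mixed model to be invalid. It is the stated justification that needs correcting, and how a null result would be read depends on it.

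**What to change.** Recompute for the enhanced-versus-basic contrast at three months. State:

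- the test, its sidedness and the assumed baseline correlation;
- the mean cluster size and expected number of clusters (440/8 = 55 to 440/3 ≈ 147; 88 at m = 5);
- an ICC range, with design effect 1 + (m − 1) × ICC or its unequal-size version;
- the expected loss at three months.

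Then restate the power or detectable effect for 440 recruited. Without baseline adjustment that is about d = 0.40 at m = 5, ICC 0.05 and 20% loss; adjustment makes it smaller, for example 0.40 × √(1 − 0.7²) ≈ 0.29 at an assumed correlation of 0.7. Reconcile the printed f² with d in the same edit. Commit to reporting the observed ICC with the results.

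The cost is a recalculation, some wording and a less favourable stated power. No additional recruitment is needed.

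### The power statement equates f² = 0.13 with d = 0.25, which are different effects, and 80% power for d = 0.25 with 440 participants in three arms does not follow from the printed inputs

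*Protocol article*

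**What the plan says.** The section Sample size and statistical power gives the error rates ("Based on sample size calculations (α = 0.05, β = 0.2") and concludes that "a sample of 440 will be sufficient to detect a small effect size (Cohen’s f^2^ = 0.13, Cohen’s d = 0.25"). It thus expresses one effect in two metrics.

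Two further statements show which comparison is meant. The pilot of the app "found a small to medium effect size difference (Cohen’s d = 0.39) relative to a waitlist control condition", and a similar difference is expected for enhanced versus waitlist. For the two app arms it says: "A smaller effect size difference is anticipated between the socially-enhanced experimental condition and the basic experimental condition, hence the larger sample size". Under Procedure, clusters are allocated "on a 1:1:1 allocation ratio".

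Under Statistical analyses, the primary outcome is to be analysed with a random effects mixed model for change across baseline, three and nine months. The sample size section names no test, sidedness, baseline to follow-up correlation, intracluster correlation or dropout rate.

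**The concern.** Two things look wrong. First, one sentence gives a single effect as two numbers that do not convert into each other, so a reader cannot tell from the sentence alone which effect the calculation used. Second, a total of 440 is modest for d = 0.25 when only two of three equal arms enter the comparison.

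The stake is the enhanced-versus-basic contrast. The primary aim under Objectives compares the enhanced app with both the basic app and the waitlist, and the Discussion singles out whether social and gamification features add efficacy. If the 80% does not apply to that contrast, the trial's most distinctive question is planned on a power that the article does not support.

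**Working it through.** **Inputs.** From Sample size and statistical power: α = 0.05 (taken as two-sided), power 0.80, N = 440, d = 0.25, f² = 0.13, pilot d = 0.39. From Procedure: three arms at 1:1:1, clusters of three to eight. Per arm: 440/3 = 146.7, about 147.

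**1. Effect-size conversion.** For two equal groups f = d/2 and f² = d²/4.
- d = 0.25 gives f = 0.125 and f² = 0.0156.
- f² = 0.13 gives f = √0.13 = 0.36 and d = 2 × 0.36 = 0.72, which is not small. A three-group F test would need only 78 participants for 80% power at that effect.
- 0.125 rounds to 0.13, so the printed 0.13 fits f.

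**2. Attempt to reproduce 80% at N = 440 for the stated effect, unadjusted and two-sided.**

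| Comparison | Power |
|---|---|
| Two arms of about 147, d = 0.25 | 57% |
| Both app arms pooled versus waitlist, d = 0.25 | 69% |
| Three-group F test, f = 0.125 | 64% |
| Three-group F test, f = 0.13 | 68% |

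For the pairwise row, the noncentrality is d√(n/2) = 0.25 × √(146.7/2) = 2.14. The normal approximation gives Φ(2.14 − 1.96) = 57%, and the noncentral t agrees. None of these gives 80%. A one-sided test of the same pair gives 69%.

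**3. What the pairwise contrast can detect.** The detectable d at 80% is (1.96 + 0.84) × √(2/146.7) = 0.33. For d = 0.25, n per arm = 2 × (1.96 + 0.84)²/0.25², about 252 by the normal approximation and 253 by the t test (756 to 759 in total). At d = 0.39, the enhanced-versus-waitlist contrast has 91% power.

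**4. Adding baseline adjustment.** This assumes that d is on the SD of the outcome and that the baseline to follow-up correlation is r. The effective effect is d/√(1 − r²). At r = 0.5 it is 0.25/√0.75 = 0.289; at r = 0.65 it is 0.25/√0.5775 = 0.329.

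**5. Adding clustering.** Assume an ICC of 0.05 and a mean cluster size of 5.5, the midpoint of three to eight. The design effect is 1 + (5.5 − 1) × 0.05 = 1.225, which leaves 146.7/1.225 = 119.7 effective participants per arm.

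| Assumed r | Power at d = 0.25, no clustering | With design effect 1.225 |
|---|---|---|
| Unadjusted | 57% | 49% |
| 0.5 | 69% | 60% |
| 0.6 | 76% | 67% |
| 0.65 | 80% | 72% |
| 0.7 | 85% | 77% |

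An assumed 20% dropout, without clustering, takes the unadjusted 57% to 48%. The values of r, ICC and dropout are assumptions; the article gives none of them.

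**The case against.** The label error looks harmless. The d beside it and the word small show which effect was meant, and correcting f² to f changes neither sample size nor analysis. That is fair, but the printed figure is still wrong.

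The stronger objection concerns the 57%. It belongs to an unadjusted comparison, and the article plans a mixed model that includes baseline. A total of about 440 can be recovered with an unstated correlation: a three-group ANCOVA at f = 0.13 and r = 0.5 needs 431, and a between-group repeated-measures test at f = 0.125 with three measurements and r = 0.55 needs 435. The full protocol or an analysis plan may hold these inputs. A reader might therefore infer from 57% that the trial is simply underpowered, or that the 80% is false; the article supports neither without that condition. What remains is that both recoveries are for a three-group test. The pairwise contrast that the section ties to the sample size still has 69% at r = 0.5.

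A further objection is that the article expects a pattern, not a single gap. With standardised means of 0.39, 0.14 and 0, f is 0.161 and the unadjusted three-group F test has 86% power. This is correct, but it is power to detect any difference among the arms, helped by the larger enhanced-versus-waitlist gap. It is not power to detect 0.25 between the two app arms.

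Two other inferences are tempting and unsupported. One is that 440 came from a two-arm calculation: 220 per arm gives 74% two-sided at d = 0.25, so that does not reproduce the claim. The other is that a null enhanced-versus-basic result would be taken as equivalence; the article proposes no such reading.

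**Conclusion.** The concern holds in two parts. The effect sizes contradict each other whatever analysis is used: d = 0.25 is f² = 0.016, and the printed 0.13 is about eight times that (0.13/0.0156 = 8.3).

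The 80% for d = 0.25 does not follow from the printed inputs. How far the true figure falls short depends on quantities that the article does not give. For enhanced versus basic, with baseline adjustment, 80% requires a correlation of about 0.65 with no loss to clustering or dropout. With the assumed clustering, power is 72% even at that correlation. If d = 0.25 is already on the change scale, as the pilot's baseline-to-follow-up description may suggest, the gain from adjustment cannot be credited in full a second time. The shortfall concerns this contrast; enhanced versus waitlist at d = 0.39 is well powered before clustering and loss.

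**What to change.** Correct the label to f = 0.125 (f² = 0.016), d = 0.25. Then replace the single power claim with the power of 440 (about 147 per arm) for each pairwise contrast under the planned mixed model. State the test, sidedness, baseline to follow-up correlation, and allowance for clustering and dropout.

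As a reference line, the unadjusted two-sided figures before clustering and loss are about 91% at d = 0.39 for enhanced versus waitlist, and about 57% at d = 0.25 (detectable d = 0.33) for enhanced versus basic. They should be labelled as unadjusted, so that they are not taken for the power of the planned model.

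The cost is wording only, with no extra participants and no change to design or analysis. The one downside is that the stated power for enhanced versus basic may be less favourable than 80%.
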